### Interventions

Our primary intervention will be a novel preventive intervention that combines psychoeducation about relationships and communication strategies, drawing on methods used in Interpersonal Therapy – Adolescent Skills Training (IPT-AST; [47]) and other comparable programmes (e.g. [46, 49]), with cognitive-emotional training that targets key emotion processing abilities implicated in the onset and maintenance of psychopathology [5, 15, 34]. We first describe the structure of the new group intervention which integrates the focus on communication with the battery of the cognitive-emotional training tasks. We then describe the structure of each of the training tasks in greater detail.

#### The ReSET group intervention

ReSET is a manualised intervention (including cognitive-emotional training elements) delivered in a group-based setting with up to 10 adolescents allocated to each group. Sessions will be held weekly over an 8-week period and each session lasts between 90 and 120 min. The sessions will focus on developing adolescents’ understanding of the links between their social relationships, emotions, and mental health. Here, we describe the structure of our intervention that integrates the cognitive-emotional training tasks with psychoeducation about communication and mental health.

The intervention will begin with young people having an individual meeting with the group facilitator to discuss the aims of the groups, their goals for taking part, and any questions they have about the sessions. These individual meetings will be used to identify where the young person may be experiencing interpersonal difficulties that can be addressed in the group sessions. Issues arising from interpersonal difficulties will be set as explicit goals by the young person (with the aid of the facilitator), which will allow the young people to self-monitor their progress throughout the duration of the intervention.

Each of the group sessions will begin with participants completing the Child Outcome Rating Scale (CORS), a clinical measure designed to monitor an individual’s progress during the therapeutic process [52, 53]. The CORS measures several domains of the young person’s life functioning, including their individual wellbeing, interpersonal wellbeing, social role, and overall wellbeing [53]. The CORS has been validated with adolescents aged 11–15 [52]. Clinical cut-offs will be used by facilitators to identify young people who may need additional support during the group, or those that may benefit from more targeted services. The CORS will also be utilised during the intervention sessions to consider links between the strategies discussed in the sessions, their impact on how participants communicate with those around them, and the relationships between social interactions and wellbeing. Drawing links between social interactions and wellbeing will be a core component of the psychoeducation content of the intervention, particularly in relation to communication.

The main body of the group sessions will include a mixture of discussion activities, role-plays, and reflective exercises. These sessions draw on principles from IPT and IPT-AST and integrate these with consideration of the role that emotion processing plays in one’s social interactions. The sessions will aim to teach participants about effective communication and emotion processing strategies that can improve social relationships and subsequently mental health. Sessions will end with participants being provided with homework to complete before the next session. The eight sessions will be structured to gradually introduce participants to the psychoeducation content and training tasks in early sessions before they are encouraged to apply the skills developed to their personal experiences.

The initial phase of the intervention will take place during sessions 1–4 (see Fig. 1). During these sessions, participants will be introduced to the cognitive-emotional training tasks and instructed how to complete them. Participants will also be introduced to the core concepts of the intervention; namely, the links between social relationships, emotion processing and wellbeing. Participants will be guided to explore the impact their emotions and responses can have on those around them, which will be used to identify opportunities to utilise adaptive communication or emotion processing skills. In sessions 2–4, participants will be provided with specific communication and emotion processing strategies designed to improve interpersonal interactions. Strategies will be introduced that either have an intra-personal focus (e.g. breathing to calm themselves down before responding) which are referred to as ‘Me Strategies’, or an interpersonal focus (e.g. picking the right time to have a conversation with another individual) which are referred to as ‘We Strategies’. Using role-plays of fictional scenarios, participants will identify moments where features of an interaction led to a dispute or difficulty and are encouraged to consider alternative ways to approach the scenario using the Me and We Strategies. The fictional scenarios that will be used in the current intervention were co-produced with a separate group of young people who did not take part in the intervention.

**Fig. 1 Fig1:**
[figure not shown]
Structure of the hybrid group intervention and research assessments

In each session, participants will complete an emotion regulation training task and in sessions 2–7 participants complete an emotion perception training task. Each of these tasks is delivered via a tablet that is provided to schools by the research team. From session 4 onwards, participants also complete breathing exercises designed to train the ability to identify one’s internal bodily signals, which is aimed at improving participants’ interoceptive abilities [54]. The intervention will include specific psychoeducational content on the features of emotion processing that the cognitive-emotional training tasks target, so that young people understand how the training relates directly to the ‘Me’ and ‘We’ strategies discussed in the group. In sessions 2–4, the group leader will facilitate activities to discuss how the cognitive-emotional mechanisms trained using the tasks (e.g. emotion perception) relate to our daily experiences, including interactions with those around us. The group facilitator will encourage participants to identify opportunities to use the skills developed through the cognitive-emotional training battery to improve their interpersonal interactions.

The middle sessions of the intervention (sessions 5 and 6) are designed to encourage participants to actively apply the ‘Me’ and ‘We’ Strategies to scenarios relevant to their lives. The scenarios that the young people discuss are intended to be relevant to the goals they identified in the individual meetings prior to the group sessions to support them to achieve these goals. The group facilitator will guide participants to reflect on conversations the participant has had and plan future interactions using the strategies outlined in sessions 1–4. The group facilitator will encourage participants to consider how different strategies can be used in combination, with the aim of providing participants with a ‘toolkit’ of adaptive interpersonal and emotion processing strategies that improve their interactions with individuals in their lives. Participants will be tasked with homework to practice conversations at home and report how these interactions went in the following session.

The closing sessions (sessions 7 & 8) of the intervention are designed to prepare participants to use these strategies independently, rather than relying on prompts from the group sessions. In these closing sessions, the group leader will review which of the communication and emotion processing skills have been useful and will work with participants to identify methods that encourage the self-generated use of these strategies outside of the sessions. During these final sessions, the young people will be asked to rate their progress on the goals they identified prior to starting the group sessions as a reflective exercise.

#### Interpretation bias training

To index and train biases in emotion perception we will utilise a task that measures participants’ subjective perception of ambiguous facial expressions. The interpretation bias training task requires a forced choice judgement as to whether the presented face is displaying an ‘angry’ or ‘happy’ expression. We will deploy an existing training protocol that has been shown to successfully shift perception from angry towards happy emotions, and significantly improve symptom outcomes in adolescents [14, 19]. On each trial the participant will be presented with a face and asked to categorise whether the emotion presented was happy or angry. There are a total of 15 facial expressions that range from unambiguously happy to unambiguously angry, with images between the unambiguous extremes linearly morphed at equal intervals from the two unambiguous emotions [55]. Stimuli will be presented for 150 ms after which a mask will be presented for 250 ms.

During the training, participants will first complete an assessment task where they are asked to make forced-choice judgements about the stimuli without receiving feedback. The assessment phase consists of 45 trials, meaning that the full stimuli set of 15 images is presented three times. Participants’ rating on the assessment task is used to calculate a ‘balance point’, which is a measure of the point within the stimuli set at which participants shift to perceiving stimuli as displaying anger rather than happiness [14, 19]. The balance point is calculated as the number of faces categorised as happy, divided by three [56]. We will introduce an attention check to identify patterns of random responding, such that participants who respond incorrectly to five of the most extreme morphs will be asked to restart the assessment task, with a prompt reminding them to pay attention to the task.

The training section of the task mirrors the structure of the assessment phase, with the addition of feedback determined using the participant’s balance point. Participants complete 90 trials in which they receive feedback that faces that are two images above their balance point along the linear continuum are categorised as ‘happy’. On training trials, participants will categorise stimuli as either happy or angry, after which they will be provided with feedback about whether they are correct, along with a visual cue indicating whether they are correct or incorrect (see Fig. 2). Feedback will be calibrated to participants’ balance point to shift their individual bias away from perceiving negative emotions. However, a threshold will be set such that the three most unambiguous faces will always be classed as the correct emotion (e.g. participants will always receive feedback that the three most angry faces are exhibiting anger). As such, there is a ceiling for the feedback participants can receive in these sessions.

**Fig. 2 Fig2:**
[figure not shown]
Negative emotion perception training task. At T1, participants are presented with a fixation cross, followed at T2 by an ambiguous facial stimulus. This facial stimulus is followed at T3 by a visual mask. At T4, participants are provided with unlimited time to make a categorical judgement about the emotion they perceived the face to be displaying. At T5, participants are provided with feedback, along with the ‘correct’ emotion. Note, the assessment task follows the same structure, but does not include the feedback screen (T5)

The emotion perception training is completed six times over the course of the intervention (in sessions 2–7). The number of training sessions was determined based on previous research (e.g. [19]) as well as pilot data which suggested that training effects asymptote by the fifth to sixth training session. Across training sessions, different avatars will be used as stimuli in the task to ensure participants are trained using individuals from diverse ethnic backgrounds and the presentation order of these avatars is randomised across participants. For each participant, the same avatar is presented for the first and final training sessions. These avatars were drawn from stimuli used in previous research [57]. Altogether, the task takes approximately 10 min to complete.

#### Emotional regulation training

The emotion regulation training is derived from tasks widely used in the literature on affective cognitive control [58] and has been modified for adolescents [59]. The task aims to train adolescents to utilise adaptive emotion regulation strategies (i.e. reappraisal and distancing) when presented with negative scenarios. Before starting the task, participants will be presented with developmentally appropriate instructions informing them about the reappraise and distance emotion regulation strategies [60]. At the start of each block participants will be instructed to use an emotion regulation strategy (either ‘reappraise’ or ‘distance’) when viewing the stimuli. After receiving instruction about which strategy to use, participants will be presented with a written scenario detailing a negative social interaction (e.g. ‘your friend ignores your text’), which lasts for five seconds. This scenario is presented both visually and auditorily, consistent with previous research [61]. The presentation of the written scenario will be followed by self-report of the strength of negative affect (see Fig. 3).

**Fig. 3 Fig3:**
[figure not shown]
Schematic outline of the emotion regulation training task. At T1, participants are presented with an emotion regulation strategy (either ‘REINTERPRET’ or ‘DISTANCE’) before being presented with a scenario designed to elicit a negative emotion (T2). At T3, participants are asked to report their affect on a Self-Assessment Manikin

The scenarios we present to participants will be selected from a mixture of those used in previous research [59] and from novel scenarios co-produced with adolescents for the purposes of this study. To develop these novel scenarios, we conducted a co-production session with 23 adolescents aged 16–17 who were asked to document negative interpersonal situations that would be relevant to adolescents aged 11–14. Following this initial session, we asked a separate group of 19 young people aged 16–17 to rate each of these scenarios using Self-Assessment Manikins (SAM; [62]). The SAM provides a pictorial representation of how the participant is feeling on different domains of affect. We asked this group of young people to rate whether the scenario made them feel unhappy (ranging from 1–5 where 1 was happy and 5 was unhappy), excited (ranging from 1–5 where 1 was excited and 5 was calm) and in control as opposed by being controlled by external forces (ranging from 1–5 where 1 was in control and 5 was controlled). As we only aimed to train young people to regulate negative emotions, we excluded any scenarios that were rated below three on the SAM rating for happiness, as this would indicate the scenario produced positive emotions.

The emotion regulation task will be split into four blocks each containing eight scenarios (32 trials in total). Each block instructs participants to use one of the emotion regulation strategies (‘reinterpret’ or ‘distance’) and are presented in alternate sequences (i.e. a reinterpret block is followed by a distance block, which is followed by a reinterpret block). The order with which the blocks are presented will be counterbalanced across sessions. We will structure the emotion regulation task such that early trials presented scenarios that were only mildly negative (as rated by the adolescent focus group) and increased in the strength of negative affect as the task progressed. At three intervals during the task, we will ask participants ‘how engaged are you feeling?’ as a measure of attention. The task takes approximately 12 min to complete.

#### Adherence

Adherence to the intervention is promoted using verbal encouragement from school contacts who will liaise between the facilitation team and study participants. School liaisons also communicate with class teachers to ensure students are released from their usual classes to attend sessions. Further, the mid-group meeting is used as an opportunity to identify any barriers to participation and, should any barriers be identified, provide additional support to increase adherence. Participants’ adherence to the researcher assessments is encouraged by remunerating participants for these sessions.

Throughout the intervention, adherence is monitored by recording attendance as well as monitoring the cognitive training data collected in each group session. This monitoring protocol includes attention measures collected during the cognitive training tasks. In the emotion regulation training task, participants are asked at three timepoints to report how engaged they were feeling to indicate their adherence to the training. For the interpretation bias training, participants are asked to repeat the first 45 trials measuring their balance point if they incorrectly identify the emotion in more than three of the extreme morphs. For example, if a participant incorrectly identifies the extreme image expressing anger as ‘happy’ more than three times, they are asked to repeat the assessment phase. We will report data on participants who are asked to repeat the assessment phase as a measure of adherence to the interpretation bias training.

Finally, at three timepoints during the intervention (group sessions 1, 2 and 5) a member of the research team conducts an audit of the group session. This process involves a member of the research team attending the session to monitor fidelity to the intervention manual, assessing whether key concepts are covered and explained using terminology described in the manual using an adherence checklist. The audits are also used to identify interpersonal dynamics within the group that may affect adherence to the intervention (e.g. challenging behaviour).

#### Intervention development

We conducted a pilot and feasibility study of the intervention prior to the main trial. During this development process, we piloted and feasibility-tested an interoception training protocol for adolescents. However, this training was not well received by adolescents in our pilot and feasibility studies, as participants did not engage with the task. Due to the low acceptability of the interoception training, this component of the cognitive training was removed from the final intervention. A paper detailing the intervention development process in full is in preparation.

## Outcomes

### Primary impact outcomes: general psychopathology and wellbeing

The two primary outcomes are psychopathology symptoms and mental wellbeing. Psychopathology symptoms will be assessed using the Total Difficulties Score of the Strengths and Difficulties Questionnaire (SDQ; [63]). Mental Wellbeing will be measured by the summary score of the Warwick and Edinburgh Mental Wellbeing Scale (WEMWBS; [64]). The primary endpoint will be the immediate post-intervention assessment point. Data for the primary impact outcomes will be collected prior to start of the intervention group, immediately after the intervention group has been completed, and 12-months from the first data collection timepoint (i.e. the data collected prior to the start of the intervention group). Note, these data collection timepoints are for participants allocated to both the intervention and control groups.

### Secondary impact outcomes

We will also include General Psychopathology, internalising problems and externalising problems as secondary outcomes based on a confirmatory factor analysis of the items from the Emotional Symptoms and Conduct Problems scales in the Strengths and Difficulties Questionnaire (SDQ; [63]) and 15 items from the Me and My Feelings measure (M&MF; [65]). The factor analysis will estimate a bifactor model as presented in Patalay et al. [66]. This model yields three factors: a general psychopathology factor (‘p-factor’), a specific factor measuring Internalising Problems, and another factor measuring Externalising Problems. We will assess the fit of this model to our data and estimate an amended model if necessary for estimation convergence or goodness of fit.

Additional secondary mental health outcomes will be obtained using the Patient Health Questionnaire (PHQ-8; [67]), and Generalised Anxiety Disorder Assessment-7 (GAD-7; [68]). The PHQ-8 and GAD-7 will be included as part of the Wellcome Trust/NIH common metrics for mental health [69]. Further, we will collect self-report measures of substance use: specifically, alcohol and drug use disorders using the Alcohol Use Disorders Identification Tests (AUDIT) and Drug Use Disorders Identification Tests (DUDIT). For the PHQ-8 and GAD-7, we will use established cut-off scores to establish caseness [70].

Sleep phenotypes relevant to mental health will be measured using a bespoke questionnaire comprised of items from the Pittsburgh Sleep Quality Index [71], several novel items designed to assess insomnia in a developmental sample (see Additional file 1: Appendix), and an item used to assess diurnal preference [72]. These items were selected based on their relevance to mental health outcomes and included items that asked participants to rate their typical bedtime and waketime, how many hours they typically slept for, and self-reported difficulties sleeping. The full set of items are reported in the Additional file 1: Appendix.

For intervention and control participants, data for the secondary impact outcomes will be collected prior to start of the intervention group, immediately after the intervention group has been completed, and 12-months from the first data collection timepoint.

### Mediating mechanisms

#### Emotion perception

To assess biases in emotion perception pre- and post-intervention, we will use two well validated tasks and one validated questionnaire. Biases in emotion perception will be assessed using the Interpretation Bias Assessment Task (see Interpretation Bias Training). However, for the purposes of assessing the efficacy of our intervention, we will not include trials where participants receive feedback about their performance. Participants’ balance point will be used as a metric of their bias to perceive negative emotions. Each participant will be presented with the same face when assessed pre- and post-intervention [57], but the avatar they are presented with will be randomised across participants. There is evidence that previous exposure to faces does not change emotion perception ratings on this task [14].

Emotion perception bias will also be assessed using the emotional intensity morphing task [73]. In this task, participants observe a face that gradually morphs to display an emotion (either sadness, anger, fear or happiness) or begins by displaying the emotion and gradually morphing to display a neutral emotion [74]. On trials where the face morphs to display an emotion, participants are asked to press the screen when they perceive the emotion, whereas on trials where the face morphs to exhibit a neutral emotion, participants are asked to press the screen when they no longer perceive the emotion. Self-report data of emotion perception biases will be collected using the attributional styles questionnaire [75].

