### Statistical methods

#### Primary outcome analysis

The primary analyses aim to estimate the effect of the intervention on two primary outcomes: psychopathology and mental wellbeing. Psychopathology will be measured as the self-reported SDQ Total Difficulties score. The other primary outcome, mental wellbeing, will be assessed by the summary score on the Edinburgh Mental Wellbeing Scale.

The primary outcome analysis will use a partially clustered mixed effects model [102], which takes into account that participants are clustered in treatment groups in the intervention arm, but not in the control arm, via a random effect for treatment groups. The model will adjust for baseline score of the outcome measure. We will additionally control for clustering of all participants within school years via a fixed effect, and for clustering within schools via either fixed or random effects (details will be specified in the statistical analysis plan). The evidence for a treatment effect will be evaluated via a two-sided *t*-test on the coefficient of the treatment indicator variable (intervention versus control group) from the mixed effects model, using a 2.5% level of significance. Analyses will be carried out in the R software (R Core Team 2021). The primary endpoint will be post-intervention (see Fig. 4).

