#### Secondary analyses

Analogous partially clustered models will be estimated for.Each primary outcome at 1-year follow-upEach secondary outcome at both end of intervention and 1-year follow-up

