#### Further analyses

Using structural equation modelling techniques, we will examine mediation of treatment effects using bootstrapped estimates of the indirect effect between treatment, mediator and outcome, as illustrated in Fig. 6 below. The mediation models will respect the clustered data structure and control for baseline outcome scores. A full analysis plan will be pre-registered on the Open Science Framework prior to the start of the analysis (see: https://osf.io/34jur/).

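### The assessment avatar is randomised between pupils but is in no stated model; adding it would protect the emotion-perception mediation estimate at almost no cost (minor)

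*Protocol article*

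**What the plan says.** Under Mediating mechanisms, Emotion perception, the protocol article says of the interpretation bias task: "Each participant will be presented with the same face when assessed pre- and post-intervention", "but the avatar they are presented with will be randomised across participants". The pupil's "balance point will be used as a metric of their bias to perceive negative emotions". Under Interpretation bias training, the balance point is the number of faces called happy divided by three, from 15 morphs each shown three times. The same section also fixes the face within a pupil during training: "For each participant, the same avatar is presented for the first and final training sessions".

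The stated models are these:

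- **Primary outcome analysis:** "The model will adjust for baseline score of the outcome measure", with terms for treatment group, school year and school.
- **Secondary analyses:** "Analogous partially clustered models will be estimated for" each secondary outcome. The Abstract counts the emotion-processing tasks among these.
- **Further analyses:** structural equation models with bootstrapped indirect effects. "The mediation models will respect the clustered data structure and control for baseline outcome scores". A full plan is to be pre-registered before analysis starts.

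The avatar appears in none of them, and the mediation text does not name the baseline mediator.

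**The concern.** Each pupil is scored on a single face, so any tendency of that face to look angrier or happier goes wholly into the pupil's score and is not averaged out. An avatar whose morphs look angrier lowers the balance point of every pupil who gets it, whatever that pupil's own bias or symptoms. By holding the face constant within a pupil, the design itself guards against differences between faces.

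Because the avatar is randomised, it is unrelated to arm and cannot bias the arm comparison. In the path from mediator to outcome, however, it acts as measurement error in a predictor and pulls the coefficient towards zero. Hypothesis 2 lists a shift towards seeing fewer faces as hostile as its first mediator, and the balance point is close to a direct count of that. A real mediated effect could therefore look weaker than it is.

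**Working it through.** The article gives no figure for between-avatar variance or for the mediated effect, so there is no stated number to reproduce. What follows is conditional algebra, then two simulations.

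**Inputs**
- s = share of balance-point variance due to the avatar, within arm. Not given; assumed 5, 10, 20 and 30%.
- Pre-post correlation of the pupil's own part: 0.5. This is assumed; it is the value that Sample size uses for the primary outcomes.
- Analysis sample: 432 (Sample size calculation).

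**Set-up.** Post score M1 = P1 + F and baseline score M0 = P0 + F. F is the avatar offset, the same at both times. Total variance is 1, Var(F) = s, Var(P) = 1 − s, Cov(P0, P1) = 0.5(1 − s). The outcome depends on P1 only.

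**Mediator-to-outcome path, observed M1, no baseline mediator.** The coefficient is multiplied by Var(P1)/Var(M1) = 1 − s, so the loss equals s.

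**Same path with M0 added.** The slope of M1 on M0 is k = 0.5(1 − s) + s = 0.5 + 0.5s. The multiplier is (1 − s)(1 − k/2)/(1 − k²). For s = 0.20: k = 0.60, and 0.8 × 0.7/0.64 = 0.875.

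**Arm effect on the balance point, adjusted for M0.** The residual variance is 1 − k² without the avatar and 0.75(1 − s) with it. The SE ratio is √[(1 − k²)/(0.75(1 − s))]. For s = 0.30: √(0.5775/0.525) = 1.049.

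| Avatar share s | Loss, no baseline mediator | Loss, with baseline mediator | SE excess, arm effect |
|---|---|---|---|
| 5% | 5% | 3.3% | 0.8% |
| 10% | 10% | 6.5% | 1.7% |
| 20% | 20% | 12.5% | 3.3% |
| 30% | 30% | 18.2% | 4.9% |

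The arm-to-mediator path is unbiased, so the indirect effect shrinks in the same proportion as the mediator-to-outcome path.

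**Large-sample simulation** (n = 400,000, six faces, true indirect effect 0.160, mediator otherwise free of error):

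| Model | s = 5% | 10% | 20% | 30% |
|---|---|---|---|---|
| Baseline outcome only | 0.153 | 0.142 | 0.128 | 0.111 |
| Plus baseline mediator | 0.155 | 0.148 | 0.140 | 0.132 |
| Baseline outcome plus avatar | 0.161 | 0.158 | 0.160 | 0.160 |
| Latent-type estimate using a second, avatar-free indicator | 0.161 | 0.158 | 0.161 | 0.161 |

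A change-score mediator gave about 0.088 at every avatar share. It is low because the change score misspecifies this model, but the avatar does not move it.

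The avatar term removes only its own share of the error. When 20% of the remaining mediator variance was occasion error and s was 20%, the estimate was 0.100 without the avatar and 0.126 with it, still short of 0.160.

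**Simulation at trial size** (432 pupils, five avatars, assumed paths 0.3 and 0.15, clustering omitted, joint significance test at 5%, no baseline mediator). Power for the indirect effect without the avatar was 80, 76, 68 and 60% at s = 5, 10, 20 and 30%. With the avatar it was 79 to 82%.

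**The case against.** The strongest reply is that the article does not claim to list every covariate of the mediation model. It gives a short description and leaves the full plan to a pre-registration that is not shown and may already include the avatar. That stands: the omission is not an error in the article.

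The second reply is that the design already controls the face by keeping it constant from pre to post. This stands in part. The shared offset cancels fully in a change score, but baseline adjustment removes only part of it.

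The third is that the article describes a latent-factor model, and for emotion perception "we will use two well validated tasks and one validated questionnaire". If the balance point is one of several indicators, and the others do not carry the same avatar offset, the face variance falls into its unique term and the path is not attenuated. This also stands, but the article does not say which indicators form the factor, so use as a single observed score remains possible.

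Last, the size is assumed throughout. Faces may hardly differ, and at a 5% share the simulated power gain is nil. Varying the avatars is explained by the wish for ethnic diversity, which does not show that their scores differ.

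A reader might infer that avatar differences are pure noise and that the planned analysis will underestimate mediation. The article does not support that. The same face is used at both times, the form of the mediator is not fixed, and the face variance is unknown.

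**Conclusion.** This is a minor point and a free improvement. The trial randomises a measurement factor that can shift the balance point, and no stated model uses it. The arm comparison is unbiased and loses at most about 5% in standard error under baseline adjustment. The mediated effect would be biased towards zero by about 5 to 30%, or about 3 to 18% with the baseline balance point included. That holds only if the balance point is an observed post-intervention mediator and avatars account for 5 to 30% of its variance. With a change score or a multi-indicator latent factor this bias disappears. The figures also rest on the assumed pre-post correlation of 0.5. The primary outcomes, the significance level and the sample size are not affected.

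**What to change.** In the pre-registered analysis plan, include the assessment avatar as a fixed categorical covariate in:

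- the arm-comparison model for the balance point;
- both the mediator and the outcome equations of the emotion-perception mediation model, together with the baseline balance point.

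Centring each balance point on the baseline mean of its avatar is an alternative. The plan should also say whether the balance point enters as an observed score, a change score or one indicator of a latent factor, since that decides whether the bias can arise.

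The cost is one line of text and one degree of freedom fewer than the number of avatars: four if there are five avatars, out of about 432 pupils. The article does not give the number used at assessment. Because the avatar is assigned at random, the covariate carries no risk of bias. No new measurement is needed, only the record of which face each pupil saw.
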